### Secondary outcomes

The first secondary outcome measurement is the change in muscle mass, determined as the change in QMLT using ultrasound from baseline to day 15 or ICU discharge if earlier. A portable ultrasound device (Sonosite S-ICU™) with a multiple frequency transducer (13-6 MHz, 6 cm) will be used to obtain muscle mass images. The method to obtain the images will be carried out as described by Tillquist and colleagues [24], with measurements completed using both minimal and maximal pressures. The first measure will be taken before randomisation, then on day 5, day 10, and at discharge or day 15 of ICU. A single-trained operator will complete all QMLT measures, and this technique has a very good intrarater reliability in both healthy populations [24] and critically ill patients [42]. The measurement will be completed on all participants, with bilateral measurements at two points; the midpoint between the Anterior Superior Iliac Spine (ASIS) and the upper pole of the patella and at the point two thirds between the ASIS and the top of the patella [22–24], the landmarks will be marked using a permanent pen. A linear measure will be taken for each point twice, with minimal pressure and maximal pressure applied and the measures will be recorded [22]. The device settings will be standardised for each measure, and bony landmarks will be used to determine if the transducer is oriented perpendicular to the muscle [24]. Each image will be stored to the hard drive of the ultrasound device and then transferred for further blinded analysis at a later date. The change in QMLT from baseline to day 5 and discharge or day 15 will be calculated for each patient for the measurements taken with minimal pressure and maximal pressure separately.

The other secondary outcomes are total calorie and protein provision, calorie deficit and protein adequacy, incidence of feed intolerance, number of days of feed intolerance, incidence of diarrhoea defined as more than three bowel actions or greater than 300 ml per day [43], length of ICU stay, hospital mortality at 28 and 60 days, discharge destination, muscle strength, the incidence of ICU AW and physical function at ICU discharge, and the change in nutritional markers over the study period. Nutritional markers include assessment of malnutrition using the Subjective Globe Assessment (SGA) [35], mid upper arm circumference (MUAC), and body weight. These measures will be carried out at baseline, day 5, and at discharge from ICU; the change from baseline to discharge or day 15 will be calculated. The presence of acute renal failure defined by the RIFLE criteria [44] and plasma urea and creatinine levels will be assessed on a daily basis.

Protein adequacy will be determined over the ICU admission or until day 15 by adding the daily protein provision and comparing this to the estimated protein requirements determined by the dietitian. The protein adequacy will then be explored in relation to the other outcome measures.

Calorie deficit will be determined using both predicted weight-based energy requirements (25 kcal/kg). In eligible patients, calorie deficit will also be calculated using measured energy expenditure (MEE) [45]. Cumulative calorie deficit will be calculated over the ICU admission or until day 15 of the study. MEE will be assessed with indirect calorimetry using E-sCOVX (GE, Helsinki, Finland) [46]. The first MEE will be within 24 h of enrolment into the study and repeated on day 3, day 5, and day 7 of the ICU stay. The measurements will be carried out with the patient in a fed state lying supine. The measure will be taken over a 2-h period, and the summary data of respiratory quotient (RQ) and MEE will be recorded. The feeding rates will not be adjusted in relation to the MEE [47]. Contraindications to carrying out a metabolic measurement will include if the patient is on continuous renal replacement therapy or extracorporeal membrane oxygenation (ECMO) or if the patient has an intercostal catheter with an air leak or is on a fraction of inspired oxygen greater than 0.6 [47].

Feed intolerance will be determined as a single gastric residual volume > 300 ml [48].

Muscle strength will be determined in suitable participants using handgrip dynamometry and the Medical Research Council (MRC) scale [49, 50]. The first muscle strength test will be performed at awakening [50] and then again at discharge or day 15, whichever comes first. Patients will be screened for attention and comprehension on the basis of their ability to follow commands, they will be considered awake if they score at least three out of five using the De jonghe comprehension criteria on at least two occasions within a 6-h period [51] and have a Riker sedation-agitation scale score of three to five [52]. Handgrip dynamometry (Commander Echo™ Wireless Grip Dynamometer, USA) will be measured in both limbs with the participant in a chair or sitting at least at 45° in bed, with the patients elbow at 90° supported by a pillow or the arm of the chair. The Medical Research Council sum score (MRC-SS) will be measured as previously described [51, 53, 54] with ICUAW defined as an MRC-SS of < 48/60 [55].

Physical function will also be assessed using the physical function in Intensive Care Test–scored (PFIT-s) [56, 57]. Patients may only be able to perform part of the test, but are still able to obtain a score.

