### Trial intervention and comparator

The intervention or standard care will be delivered following randomisation until ICU discharge; the patient no longer requires enteral tube feeding, or at the end of day 15, with the day of randomisation being day 1. Tolerance of enteral nutrition will be assessed and managed similarly for both groups, with prokinetic drugs (metoclopramide 10 mg q.i.d. and erythromycin 200 mg b.d.) administered if gastric residue volumes at any time equal or exceed 300 ml [38]. The need for parenteral nutrition will be determined by treating clinical staff that are not investigators and are not aware of group allocations.

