All secondary outcomes will be regarded as exploratory and hypothesis-generating, with no multiple comparison adjustment to conventional 5% type 1 error thresholds. Group differences for change from baseline at selected time points in continuous outcome variables, including QMLT, will be compared after adjustment for initial values using analysis of covariance (ANCOVA) regression models, initially unadjusted, and subsequently adjusted as described below for other regression models. Natural logarithmic transformations may be applied to stabilise variance within these or other linear models if appropriate. The relationships between calorie deficits using both prescribed calories (25 kcal/kg) and MEE and protein adequacy and the outcome measures (QMLT change, muscle strength, diagnosis of ICUAW, and physical function at ICU discharge) will be explored using linear or logistic regression analyses, with adjustment for likely confounders and any baseline variable found to show substantial imbalance between treatment groups. Finally, a population-averaged generalised linear model using a generalised estimating equation (GEE) approach with an unstructured working correlation matrix and robust standard error estimates adjusted for clustering within individual subjects will be applied to these longitudinal data to evaluate the overall associations of the vector of (untransformed or log transformed) outcome variables with treatment group across multiple time points. Multiple imputations for missing data may be used to support conclusions from other generalised linear models constructed without imputation of missing data. Data analysis will be carried out using the Statistical Package for the Social Sciences (SPSS) (IBM® SPSS® Statistics Premium Grad Pack Version 22.0) or Stata Corporation (Stata Statistical Software: Release 15. College Station, TX: StataCorp LP; 2017).

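### The exploratory regression of QMLT change on cumulative calorie deficit can show an association that comes only from days in ICU

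*Protocol article*

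**What the plan says.** All places are in the protocol article.

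- **Outcome.** Secondary outcomes defines the first secondary outcome as "change in QMLT using ultrasound from baseline to day 15 or ICU discharge if earlier". The scans after baseline are taken "then on day 5, day 10, and at discharge or day 15 of ICU". A change to day 5 is also to be calculated.
- **Exposure.** The same section says "Cumulative calorie deficit will be calculated over the ICU admission or until day 15 of the study". This is a sum, not a daily mean.
- **Analysis.** Statistical analysis plans regression models, linear or logistic, for "The relationships between calorie deficits using both prescribed calories (25 kcal/kg) and MEE and protein adequacy and the outcome measures" (QMLT change among them). On covariates it says only "with adjustment for likely confounders and any baseline variable found to show substantial imbalance between treatment groups".
- **Day count.** Trial intervention and comparator counts study days "with the day of randomisation being day 1".
- **Status.** Statistical analysis treats every secondary outcome as exploratory. The fifth secondary aim asks whether the intervention alters ICU duration and deaths.

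**The concern.** Outcome and exposure accumulate over one patient-specific window. A patient scanned last on day 5 has had few days in which to lose muscle and few days in which to build up a deficit. A patient scanned on day 15 has had three times as many of both. Across patients, a larger cumulative deficit will therefore go with greater muscle loss even when the deficit per day is unrelated to the loss per day.

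The Discussion calls the assessment of nutrition's impact on muscle mass and function essential for planning a larger multicentre study. An association that is only length of stay could be carried into that trial's rationale as a sign that underfeeding costs muscle.

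**Working it through.** **The plan's own figure.** The article gives no figure on this point. Its QMLT power statement (28 per group, difference 0.5 cm, SD 0.6 cm) reproduces: t-based power is 0.865, which is over 80%. It does not bear on the question.

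**Model with no true link.** For each patient let D be the days observed, d the daily deficit and L the daily muscle loss, all independent, and let e be scan error with SD s. Then cumulative deficit = D·d and QMLT change = −D·L + e, which gives

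- Cov = −E[d]·E[L]·Var(D)
- Var(cumulative deficit) = E[D²]·Var(d) + E[d]²·Var(D)
- Var(change) = E[D²]·Var(L) + E[L]²·Var(D) + s²

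The covariance is zero only if stay does not vary, mean deficit is zero or mean loss is zero.

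**Inputs.** n = 60 is from the article. The rest is assumed: mean d 600 kcal with SD 200 or 400; L 0.03 cm/day (SD 0.015) with s = 0.10 cm, or L 0.02 cm/day (SD 0.02) with s = 0.15 cm; D uniform over whole days.

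**Worked case, widely spread stays (D from 4 to 15).** Mean D = 9.5, Var(D) = 143/12 = 11.92, E[D²] = 102.17. With SD(d) = 200 and the first loss setting:

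- Cov = −600 × 0.03 × 11.92 = −214.5
- SD(cumulative deficit) = √(102.17 × 200² + 600² × 11.92) = 2894 kcal
- SD(change) = √(102.17 × 0.015² + 0.03² × 11.92 + 0.10²) = 0.209 cm
- r = −214.5 / (2894 × 0.209) = −0.35

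With n = 60, |r| above 0.254 is significant at 5%, so this case rejects in most trials.

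**Worked case, narrow spread (D from 10 to 15).** Var(D) = 35/12 = 2.92, E[D²] = 159.17. With SD(d) = 400 and the second loss setting, r = −35.0 / (5149 × 0.296) = −0.02, which is negligible.

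**Simulation, 2,000 trials per setting, true association zero.** Each row spans four settings.

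| Days observed | Mean r, cumulative deficit | False positives, cumulative | False positives, mean daily | Cumulative plus days as covariate |
|---|---|---|---|---|
| 4–15 | −0.35 to −0.13 | 19–81% | 5–6% | 9% |
| 7–15 | −0.20 to −0.06 | 9–37% | 4–5% | 6–7% |
| 10–15 | −0.09 to −0.02 | 6–10% | 4–6% | 5–6% |

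**A second set of assumptions (3,000 trials).** A given share of patients reaches day 15 and the rest stay 4 to 14 days; daily deficit is 600 (SD 300) kcal; loss is 2% (SD 1.5%) of 1.3 cm per day.

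| Share reaching day 15 | s = 0.05 cm | s = 0.12 cm | s = 0.30 cm |
|---|---|---|---|
| 20% | 45% | 39% | 21% |
| 60% | 24% | 22% | 14% |
| 80% | 11% | 10% | 8% |
| 90% | 7% | 7% | 6% |

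With s = 0.05 cm and a shortest stay of 8 days instead of 4, the 45% and 24% fall to 12% and 10%. Mean daily deficit rejects in 4–6% throughout.

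**Arm comparison, no true effect on daily loss (base stay 6–15 days).** With equal stays in the two arms, the mean difference is 0.00 cm and rejection is 5–6%. If the intervention arm stays 2 to 4 days less, a false difference of 0.04 to 0.12 cm appears in its favour, with rejection of 8–64%. By hand, 2 days × 0.02 × 1.3 cm = 0.052 cm, about a tenth of the 0.5 cm in the Sample size section.

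**The case against.** Several points on the other side carry weight.

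- **The covariate clause is open.** Days observed could count as a likely confounder, and naming covariates is commonly left to the analysis plan. This stands in part. Days observed cannot enter as an imbalanced baseline variable, and the confounder wording does not commit to it. Even with days added, the cumulative sum rejects in 5–9%. The exposure itself is what the article fixes badly.
- **The size rests on assumptions.** This stands. If most patients reach day 15 the problem is small, and no single percentage should be quoted as the error rate of this trial.
- **The analyses are exploratory, in a pilot of 60.** This stands and limits the weight of the point. The co-primary outcomes are daily means and lie outside it.

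Three stronger readings are tempting, and the document does not support them.

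- A reader might infer that the variable window already biases the arm comparison. In a randomised trial it does so only if stay or early death differs by arm. The fifth secondary aim leaves that open but does not establish it; otherwise the window adds noise. A fixed day-5 change is also planned.
- A reader might extend the point to protein adequacy. The article says "Protein adequacy will be determined over the ICU admission or until day 15", but by comparing summed provision with estimated requirement. Read as a ratio over the same days, it does not grow with stay.
- A reader might conclude that the planned GEE is invalid because discharge and death end follow-up. The article allows supporting multiple imputation, and a mixed model would not by itself resolve truncation by death. The choice between the two is largely a trade-off.

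**Conclusion.** The point holds for the regression of QMLT change on calorie deficit. Both variables accumulate over the same patient-specific window and no term for days observed is named, so a negative association can arise with no true link. The direction follows from the definitions, given that muscle is lost and a deficit accrues on an average day. The size depends on the spread of stay, which the article does not give: false positives are about 6% when stays are 10 to 15 days or 90% of patients reach day 15, and 45% or more in the more extreme settings with widely spread stays. Mean daily deficit gives about 5%.

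For the arm comparison the point is conditional: bias arises only if stay or early death differs by arm.

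The day count is a separate small inconsistency. The scan schedule refers to an ICU day, while the intervention and deficit windows use study days from randomisation. If randomisation falls about two days into the ICU stay (an assumption), the last scan and the end of the deficit window would be about two days apart. The passages must be reconciled.

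This is a worthwhile but modest correction to exploratory secondary analyses.

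**What to change.** 1. In the regressions on QMLT change, replace cumulative calorie deficit with mean daily deficit, or deficit as a percentage of requirement, over the interval between the scans being compared. For example, relate intake from randomisation to day 5 to QMLT change from baseline to day 5. Include the number of days in the interval as a covariate. Cumulative deficit can still be reported descriptively.
2. For the arm comparison, make the already planned day-5 change, and a day-10 change from the planned scan, the main QMLT contrasts. Report change to discharge or day 15 alongside them, with the days observed in each arm.
3. State all scan times and intake windows in one day count, and reconcile the ICU-day wording with the study-day definition.

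The cost is wording only: daily intake and the day-5 and day-10 scans are already to be collected. The downside is that the fixed-day contrasts cover a shorter period than change to day 15, and fewer patients will still be in ICU for the day-10 scan.

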### Sample size

A sample size of 60 is based on observational data [45], where daily protein intake, mean (SD), was 50.8 g (20.1 g) protein per day; therefore, 29 participants per group will provide 80% power (two-sided *α* 0.05) to detect a minimum difference of a 15-g protein between groups. While there is limited data on change in muscle mass using ultrasound, using the data from the VALIDUM study, mean (SD) QMLT of 1.3 (0.6) cm [22], a sample size of 28 participants in each group will also provide over 80% power to detect a mean difference of 0.5 cm in QMLT.

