### Statistical analysis

All analyses will use an intention-to-treat approach. Baseline patient demographics, severity of illness, ICU length of stay, mortality, and nutritional markers will be tabulated according to the treatment group. Initial exploratory data analysis will involve calculation of summary statistics and comparison between treatment groups using non-parametric (Wilcoxon), parametric (*t* test), and Fisher’s exact tests as appropriate, as well as construction of trajectory plots according to the treatment group. The co-primary outcomes of average daily energy and protein delivery will be compared between treatment and control groups with two-sample unpaired *t* tests, with statistical significance for each set conservatively at two-sided values of 0.025 to limit the family-wise type 1 error for the two co-primary outcomes to less than 0.05 overall.

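### The 80% power claim for protein uses alpha 0.05, but the protein test will be run at 0.025, where power for the 15 g difference is about 70–72%

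*Protocol article*

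**What the plan says.** The Sample size section bases the trial of 60 on protein, one of the two co-primary outcomes. It takes from observational data that "daily protein intake, mean (SD), was 50.8 g (20.1 g) protein per day". It then says that "29 participants per group will provide 80% power" at a two-sided alpha of 0.05 "to detect a minimum difference of a 15-g protein between groups".

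The Statistical analysis section fixes the test of the co-primary outcomes. Average daily energy and protein "will be compared between treatment and control groups with two-sample unpaired *t* tests", "with statistical significance for each set conservatively at two-sided values of 0.025". The stated purpose is "to limit the family-wise type 1 error for the two co-primary outcomes to less than 0.05 overall".

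The Sample size section does not mention 0.025, and nothing elsewhere in the article reconciles the two levels. No power is given for energy.

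**The concern.** The two sections use different significance levels for the same test. If protein must reach p < 0.025 to count as a success, power calculated at 0.05 is too high for it.

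The split into two tests at 0.025 makes sense only if success on either outcome is enough. If both had to succeed, no split would be needed. So the protein test has to pass 0.025 on its own, and its power should be stated at that level.

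This matters because the primary aim is whether delivery increases, and the article says that the results will help to formulate larger trials. If protein misses significance, readers will judge that result against a claimed 20% type II error that the design does not have.

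**Working it through.** **Inputs, all from the protocol article**

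- Difference δ = 15 g/day, SD σ = 20.1 g/day, 29 per group, alpha 0.05 two-sided, power 80% (Sample size).
- Unpaired two-sample t test at two-sided 0.025 for each co-primary outcome (Statistical analysis).
- Allocation 1:1, total 60, so 30 per group if the arms come out equal (Abstract; Randomisation and blinding).

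**Step 1: reproduce the stated figure at alpha 0.05**

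Normal approximation: n per group = 2(σ/δ)²(z₁₋α/₂ + z₀.₈₀)².

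With (20.1/15)² = 1.7956 and z-values 1.960 and 0.842, n = 2 × 1.7956 × (2.802)² = 28.2, rounded up to 29. This is the plan's figure.

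Exact t test: the noncentrality parameter is δ/(σ√(2/n)) = 15/(20.1 × √(2/29)) = 2.842, with 56 degrees of freedom. The critical value at 0.05 is 2.003, and power is 79.7%. The stated 80% reproduces at its own alpha.

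**Step 2: repeat at the level the trial will use**

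The noncentrality is still 2.842, but the critical value at 0.025 rises to 2.303. Power falls to 70.4%. For 30 per group the noncentrality is 15/(20.1 × √(2/30)) = 2.890 with 58 degrees of freedom.

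| Per group | Method | Power at 0.05 | Power at 0.025 |
|---|---|---|---|
| 29 | t test | 79.7% | 70.4% |
| 29 | normal approximation | 81.1% | 72.6% |
| 30 | t test | 81.1% | 72.1% |
| 30 | normal approximation | 82.4% | 74.2% |

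**Step 3: what 80% power at 0.025 would require**

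- Normal approximation: n = 2 × 1.7956 × (2.241 + 0.842)² = 34.1, so 35 per group (70 in total).
- t test: 35 per group gives 79.5% and 36 gives 80.7%, so 36 per group (72 in total).
- With the sample size unchanged, the difference detectable at 80% power is 16.6 g with 29 per group and 16.4 g with 30.

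**Not affected.** The muscle-thickness power statement (28 per group) concerns a secondary outcome, and secondary outcomes are tested at 5%.

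**The case against.** Four points can be made for the plan.

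- **The calculation is right for the alpha it states.** True: Step 1 reproduces it. The fault is an inconsistency between two sections, not a slip of arithmetic within one. The stated power is still not that of the planned test.
- **This is a pilot, and the test remains valid.** Also true. Family-wise error is controlled, the plan itself calls the threshold conservative, and no estimate is biased. But the authors chose formal tests with a power claim, and that claim should describe those tests.
- **The real difference may well exceed 15 g.** The arms are prescribed 1.0 and 1.5 g/kg. Assume that control delivery is 50.8 g and that both arms receive the same fraction of target. The expected gap is then 50.8 × 0.5 = 25.4 g. With 30 per group at 0.025, power is 99% at SD 20.1 g, and 83% if the SD is 50% larger (30.15 g). At a 17.5 g gap and SD 20.1 g it is 85.5%. This limits the practical harm. The gaps are assumptions, however, and the Background warns that intolerance could reduce delivery. The plan makes its claim at 15 g, and there it fails.
- **A Bonferroni split is a legitimate choice.** It is, so changing the testing procedure is optional. Holm alone would not make the 80% statement true, because protein's power would then depend on the energy result, for which the article gives no assumptions.

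The chance of success on at least one outcome cannot be below protein's own power. But the plan's claim is about protein specifically.

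**Conclusion.** The concern holds. On the plan's own inputs, the protein test has 70.4% power (29 per group) to 72.1% (30 per group) for a 15 g difference, not 80%. The type II error at that difference is 28–30%. Every variant calculated at 0.025, including the normal approximation at 72.6–74.2%, is clearly below 80%. Enrolling 60 rather than 58 recovers less than two percentage points.

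The figures assume an SD of 20.1 g in both arms, equal group sizes and complete data. The article specifies simple randomisation, so the arms may not be exactly equal, and any imbalance would lower power a little further. Nothing can be said about power for energy, because no inputs are given. The error leaves the validity of the primary test intact, but the headline power statement is wrong as written and must be corrected.

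**What to change.** **Required.** In the Sample size section, state that at two-sided 0.025 the 60 patients give about 70–72% power for a 15 g difference, or 80% power for about 16.5 g. This is a change of wording and needs no extra patients. Its cost is a less favourable power figure.

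**Worth adopting.** In the Statistical analysis section, replace the fixed 0.025/0.025 split with Holm's step-down procedure: test the smaller p-value against 0.025 and, if it passes, the other against 0.05. Family-wise error stays at 0.05 and power is never lower than with the fixed split. The corrected power statement is still needed.

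**Only if the 80% claim is to be kept.** Test protein first at 0.05, and test energy at 0.05 only if protein succeeds. This restores about 80–81% power for protein. The cost is that energy becomes conditional on protein and loses its equal co-primary standing.

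Screening began in August 2015 and the article appeared in February 2018. Any change to the decision rule should therefore be dated, justified and made before results by treatment group are known. A late change made to protect a power claim will draw questions; the required wording correction carries no such cost.
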